## **16.8 Interim Analyses**

Two interim analyses are planned. Firstly, after the BCR-ABL/ABL ratio 7 months after randomization is available for all patients still under study and secondly, after the BCR-ABL/ABL ratio 13 months after randomization is available for all patients still under study. Accordingly, the first and second hypotheses will be tested, respectively. At the final analyses, hypotheses 3 and 4 will be tested.

## 16.9 Analyses of “off study follow-up”

Molecular relapse-free survival (RFS) will be reported at the three fixed times, 36, 48, and 60 months after randomization. Again, at the final post study follow-up analysis, molecular RFS will also be analysed as a time-to-event variable.

### Secondary endpoints

As before, overall survival probabilities will also be estimated at the final post study follow-up analysis.

The type of current treatment for CML will be described.

Demographic data including treatment history and relevant medical history (secondary malignancies, cardiac disease, auto-immune disease, progression of CML) will be compared between arm A and B in a descriptive manner.

## 16.10 Sample Size Calculation

Molecular relapse-free survival (RFS) will be tested at three fixed times, 7, 13, and 25 months after randomization. In arm B, without any treatment after stopping TKI, the probabilities of molecular RFS at 7, 13, and 25 months are assumed to be 55%, 50%, and 45%. At each time, an increase by an absolute value of 20% in arm A is expected. At all three times, confirmatory testing is intended. To avoid an inflation of type I error, the hypotheses are put in hierarchical order. At all times, a power of 80% is planned. It is a characteristic of the binomial distribution that the variance is the higher, the nearer the probabilities are to the level of 50%. Accordingly, sample size estimation needs to be based on the assumptions at 25 months.

Patients in the standard arm B are expected to have a molecular relapse-free survival probability of 45% 24 months after discontinuation of TKI treatment. In the investigational arm A, we expect that the molecular RFS probability after 24 months of discontinuation of TKI can be increased by 20% as compared with the standard arm. Accordingly, 192 patients need to be randomized 1:1 to be able to reject the null hypothesis of same relapse-free survival probabilities with a two-sided uncorrected chi-square test at a significance level of 0.05 and a power of 80%. With an expected drop-out of 10%, the 1:1 randomization of 214 patients is necessary. The sample size calculation was performed with the program “PS Power and Sample Size Calculations”, Version 3.1.2 (Dupont WD et al., Controlled Clin Trials, 1997).

The hierarchical ordering of the hypotheses will be in accordance with the chronological ordering of the times. Assuming that all drop-outs will occur before 6 months (the most adverse case), 192 patients would be ready for analysis. With these 192 patients randomized 1:1, a molecular RFS probability of 55% at 7 months in arm B and of 75% in arm A, we would be able to reject the null hypothesis of same relapse-free survival probabilities with a two-sided uncorrected chi-square test at a significance level of 0.05 with a power of 83%.

With 192 patients randomized 1:1, a molecular RFS probability of 50% at 13 months in arm B and of 70% in arm A, we would be able to reject the null hypothesis of same relapse-free survival probabilities with a two-sided uncorrected chi-square test at a significance level of 0.05 with a power of 81%.

Apart from testing three hypotheses at fixed times, molecular RFS probabilities are investigated over time. Accordingly, molecular RFS will also be analyzed as a time-to-event variable. Assuming exponential survival times, an RFS probability of 45% at 25 months corresponds to a hazard of 0.0333 and a median survival time of 20.82 months. With an RFS probability of 65%, the hazard in the experimental arm A is 0.0179 and the hazard ratio of arm B to arm A is 1.8603. Of course, the assumption of exponential distributions does not fit – we will rather have more molecular relapses earlier, meaning higher hazards in both arms. Thus, if we assess power on the assumption of

exponential distributions, we will most likely end up with an estimation of a minimum power to be expected. It is further assumed that testing will be performed only after all patients had their minimum follow-up of 25 months. Again, being cautious in avoiding overestimation of power, accrual time was set to 0 months – this in accordance with the assumption that hardly any molecular relapse will occur after 25 months. Under all these assumptions and with 192 evaluable patients randomized 1:1, the power to reject the hypothesis of same molecular RFS probabilities with the log-rank test will be (slightly above) 80%. Again, sample size calculation was performed with the program “PS Power and Sample Size Calculations”, Version 3.1.2

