## 16 Statistical Considerations

### 16.1 Hypotheses

Four hypotheses are tested in hierarchical order. To avoid inflation of type 1 error (false rejection of a null hypothesis), further confirmatory testing has to be stopped as soon as a null hypothesis could not be rejected. All four hypotheses are tested at significance level 0.05.

At first,

Null hypothesis 1: “The probability of molecular relapse-free survival (RFS) 7 months after randomization / 6 months after stopping TKI is not different between the two arms A and B”

is tested against the

Alternative hypothesis 1: “The probability of molecular RFS 7 months after randomization / 6 months after stopping TKI is different between the two arms A and B”.

In case null hypothesis 1 can be rejected,

Null hypothesis 2: “The probability of molecular RFS 13 months after randomization / 12 months after stopping TKI is not different between the two arms A and B”

is tested against the

Alternative hypothesis 2: “The probability of molecular RFS 13 months after randomization / 12 months after stopping TKI is different between the two arms A and B”.

In case null hypothesis 2 can be rejected,

Null hypothesis 3: “No difference in the molecular RFS probabilities between the two arms A and B at any time”

is tested against the

Alternative hypothesis 3: “Molecular RFS probabilities between the two arms A and B are different”.

In case null hypothesis 3 can be rejected,

Null hypothesis 4: “The probability of molecular RFS 25 months after randomization / 24 months after stopping TKI is not different between the two arms A and B”

is tested against the

Alternative hypothesis 4: “The probability of molecular RFS 25 months after randomization / 24 months after stopping TKI is different between the two arms A and B”.

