### Primary efficacy endpoint

The four hypotheses will be tested in hierarchical order, see above. Null hypotheses 1, 2 and 4 will be tested with the two-sided, uncorrected chi-square test. Null hypothesis 3 will be tested with the two-sided log-rank test. The result of BCR-ABL ratio according to the IS needs to be observed. In case of null hypotheses 1, 2, and 4, the BCR-ABL ratio according to the IS has to be available. For the times 6, 12, and 24 months after stop of TKI (i.e. 7, 13, and 25 months after randomization), a time interval around the corresponding time is allowed. Each result should be relatable to exactly one of the visits scheduled in the protocol. Accordingly, intervals are defined by the time in the middle between two visits (schedule of visits see e.g. study flow chart). As visits are scheduled 6, 7, and 8 months after randomization, the interval for relating a result to the 7-month visit is given by 6.5 to 7.5 months after randomization. With visits planned 11, 13, and 15 months, the interval for relating a result to the 13-month visit is given by 12 to 14 months, and finally, with visits foreseen 24, 25, and 36 months after randomization, the result should be recorded within the interval from 24.5 to 30.5 months after randomization. In case of more than one observation within an interval, the approach of Pffirmann et al. will be chosen in order to determine the decisive result. In case of the observation of an extremely unfavourable result prior to the upper time limit of an interval, this result will be carried forward and will be rated as “no MMR/relapse”. Extremely unfavourable results are accelerated disease, blast crisis, or death from any cause. Details on the outcome will be reported. For analyzing null hypothesis 3, it is important to ensure that the BCR-ABL ratio is evaluated at all times foreseen in Table 1. Accelerated disease and blast crisis imply a prior loss of MMR. Molecular RFS probabilities over time will be described by Kaplan-Meier estimates. RFS probabilities over time will be compared by the log-rank test.

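### The planned 80% power at every time point holds for each test alone, but not for the confirmatory 25-month test (H4) reached through the fixed hierarchy

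*Protocol*

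**What the plan says.** Section 16.1 lists four hypotheses in fixed order: RFS at 7 months (H1), RFS at 13 months (H2), RFS over time (H3) and RFS at 25 months (H4). The rule is that "further confirmatory testing has to be stopped as soon as a null hypothesis could not be rejected", and "All four hypotheses are tested at significance level 0.05". Under Methods of Analysis (16.7), "Null hypotheses 1, 2 and 4 will be tested with the two-sided, uncorrected chi-square test" and "Null hypothesis 3 will be tested with the two-sided log-rank test".

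Section 16.10 gives the planning values. In arm B "the probabilities of molecular RFS at 7, 13, and 25 months are assumed to be 55%, 50%, and 45" percent, and "At each time, an increase by an absolute value of 20% in arm A is expected". It says that confirmatory testing is intended at all three fixed times and that "At all times, a power of 80% is planned". It derives 192 evaluable patients (214 randomized at 10% drop-out) from the 25-month values. With 192 patients it reports 83% power for H1, 81% for H2 and slightly above 80% for the log-rank test. It describes 192 evaluable at the first look as the most adverse drop-out case.

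For the log-rank test the same section takes 45% RFS at 25 months, a hazard of 0.0333, a median of 20.82 months and an arm A hazard of 0.0179, and concludes that "the hazard ratio of arm B to arm A is 1.8603".

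**The concern.** The section uses the hierarchy to protect the type I error and to fix the order of tests, but not when it speaks of power. Under the rule in 16.1, H4 can be rejected in a confirmatory sense only if H1, H2 and H3 have been rejected first. Its chance of success is therefore a joint probability. Since H4 alone has 80% and the sample size was set to give just that, the joint figure must fall below 80%.

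This matters most for H4. Arm A receives AOP2014 until month 15 and is then observed untreated for 10 months (section 8.2.4). H4 is thus the only fixed-time confirmatory comparison made after the drug has been withdrawn, and section 8.2.4 itself rests the judgment of efficacy on month 25. A reader of 16.10 would put the risk of missing it under the planned effect at 20%.

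**Working it through.** **Inputs (16.1, 16.4, 16.7, 16.10).** RFS at 7/13/25 months is 55/50/45% in arm B and 75/70/65% in arm A. Alpha is 0.05 two-sided, with 96 evaluable per arm. RFS is a first-event time, so a relapse at one time point stays a relapse at later ones.

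**Step 1: stand-alone powers.** For the uncorrected chi-square test, power = Φ(u), with u = [0.20 − 1.96·√(2p̄(1−p̄)/n)] / √{[pA(1−pA)+pB(1−pB)]/n}.

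- H1: (0.20 − 0.1349)/0.0673 = 0.967, power 83.3%.
- H2: (0.20 − 0.1386)/0.0692 = 0.887, power 81.2%.
- H4: (0.20 − 0.1407)/0.0703 = 0.842, power 80.0%.
- H3, exponential: expected events 96 × (0.55 + 0.35) = 86.4 and HR 1.854 give 81.8% (Schoenfeld) or 79.4% (Freedman).

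The sample size of 96 per arm, and 192/0.9 rounded up to 214, also reproduce. The printed figures are right for single tests.

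**Step 2: correlation between time points.** For t1 ≤ t2 the covariance of the estimated differences is the sum over arms of S(t2)[1 − S(t1)]/n.

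- 7 and 13 months: (0.70·0.25 + 0.50·0.45)/√(0.435·0.460) = 0.400/0.447 = 0.894.
- 7 and 25 months: (0.65·0.25 + 0.45·0.45)/√(0.435·0.475) = 0.365/0.455 = 0.803.
- 13 and 25 months: (0.65·0.30 + 0.45·0.50)/√(0.460·0.475) = 0.420/0.467 = 0.899.

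**Step 3: power through the hierarchy, 96 per arm.** The multivariate normal with these correlations gives 77.4% for H1 and H2 together, and 72.9% for H1, H2 and H4. One million simulated trials of the chi-square tests give 77.4% and 73.0%.

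Adding the log-rank step needs a curve between the time points. Constant hazards between the planning values, starting at month 0 or month 1, give (40,000 trials each):

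| | Stand-alone | Through the hierarchy |
|---|---|---|
| H2 | 81% | 77.1-77.8% |
| H3 | about 84% | 75.3-76.1% |
| H4 | 80% | 72.6-73.3% |

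**Step 4: drop-out timing** (chi-square steps only; evaluable numbers per arm at 7/13/25 months are assumed):

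| Evaluable per arm | H2 | H4 |
|---|---|---|
| 96/96/96 | 77% | 73% |
| 104/101/96 | just above 80% | 74% |
| 107/107/96 | 82% | 75% |
| 107/107/107 (no drop-out) | 82% | 78% |

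Reaching 80% for H4 through the chi-square steps takes about 112 evaluable per arm (80.2%), that is 224, or about 249 randomized at 10% drop-out. The log-rank step would raise this slightly.

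**Step 5: log-rank inputs.**

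- At 25 months: −ln(0.45)/25 = 0.0319, −ln(0.65)/25 = 0.0172, median ln 2/0.0319 = 21.7 months.
- At 24 months: 0.0333 and 0.0179, median 20.83 months. The printed 20.82 is ln 2/0.0333, from the rounded hazard.
- The ratio is ln(0.45)/ln(0.65) = 1.854 on either time scale. The printed 1.8603 is 0.0333/0.0179.

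Power = Φ(√{n(ln HR)²/(1/pA + 1/pB)} − 1.96), where pA and pB are event probabilities. The printed hazards over 24 months give 80.3%; the 25-month hazards over 25 months give 79.9%. Running the printed 24-month hazards over the stated 25 months of follow-up would give 81.4% (pA 0.361, pB 0.565).

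**The case against.** The strongest reply is that no printed power is wrong. Section 16.10 ties each figure to one named test with 192 patients, and each reproduces. The protocol never claims 80% for passing the whole chain. The primary endpoint is RFS at 7 months; RFS at 13 and 25 months are listed as secondary endpoints of a phase II trial. All of this stands, and it is why the point concerns a missing qualifier rather than a miscalculation. It does not remove the point: the planned 80% is stated for all times, directly after confirmatory testing has been announced for all three, and nothing says that it leaves the hierarchy out.

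A second reply is that 192 evaluable patients at every look is a floor. This also stands. Later drop-out lifts H2 to 80% or more. H4 stays below 80% in every case examined, including no drop-out at all.

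A third reply is that the log-rank slip is immaterial and that relabelling the time scale cures it as well as new hazards would. That is correct: section 16.10 itself also gives the 45% as a value 24 months after stopping TKI.

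A reader might infer that the trial is underpowered for its primary question, that the design simply delivers 73%, or that the sample size must rise. The documents support none of these. H1 comes first and keeps its 83%, and 73% belongs to the protocol's most adverse drop-out case. Nor should an H3 stand-alone power of about 80% be set beside 75% through the hierarchy as if the gap were the cost of the ordering. The first comes from the exponential model, which section 16.10 calls a likely minimum; the second comes from a front-loaded curve whose stand-alone power is about 84%.

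**Conclusion.** The point holds for the later confirmatory tests, and chiefly for H4. Under the protocol's own RFS values, the probability of a confirmatory rejection at 25 months is about 73% with 192 evaluable patients and about 78% with no drop-out, against a planned 80%. The chance of missing it under the planned effect is thus about 22-27%, not 20%. For H2 the range is about 77-82%, so its shortfall depends on drop-out timing. For H3 it is about 75-76% with 192 evaluable.

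The H2 and H4 figures rest on the planning values, on relapse being a lasting event and on non-informative drop-out. The H3 figure also rests on the assumed curve between visits. The hazard inputs are wrong as labelled, but with hazards and follow-up on the same time scale the effect on power is under half a point.

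**What to change.** In section 16.10, replace the sentence on planned power with wording such as: the powers of 83%, 81%, about 80% and 80% apply to H1, H2, H3 and H4 each tested alone with 192 evaluable patients; under the hierarchical procedure the probability of confirmatory rejection is about 77-82% for H2 and about 73-78% for H4, depending on the timing of drop-outs. If H3 figures are given, take the stand-alone and the hierarchical value from the same survival model.

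Separately, make the log-rank inputs consistent. Either relabel 0.0333, 0.0179 and about 20.8 months as 24-month values with matching follow-up, or use 0.0319, 0.0172 and 21.7 months for 25 months. The hazard ratio is 1.854 in both cases.

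The cost is a few restated sentences. No test, significance level, analysis population or data item changes, and N need not change.

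### The 80% power claimed at every time point ignores the fixed testing sequence: H2, H3 and H4 have about 77%, 75% and 73%

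*Protocol*

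**What the plan says.** Section 16.1 orders four hypotheses: RFS at 7 months (H1), RFS at 13 months (H2), RFS over time (H3) and RFS at 25 months (H4). The rule is that "further confirmatory testing has to be stopped as soon as a null hypothesis could not be rejected", and "All four hypotheses are tested at significance level 0.05". Section 16.7 adds: "Null hypotheses 1, 2 and 4 will be tested with the two-sided, uncorrected chi-square test" and "Null hypothesis 3 will be tested with the two-sided log-rank test".

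Section 16.10 says "At all three times, confirmatory testing is intended" and then "At all times, a power of 80% is planned". It bases the sample size on month 25 (45% against 65%), which gives 192 evaluable patients and 214 randomized after allowing for 10% drop-out. With 192 evaluable it reports power of 83% at 7 months, 81% at 13 months and 80% at 25 months, and puts the log-rank power slightly above 80%. The hierarchy is mentioned there only as protection of the type I error. It is not carried into any power figure, and no figure is marked as applying to one test in isolation.

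**The concern.** Under a stop-at-first-failure rule, the power to confirm a later hypothesis is the joint probability of rejecting it and every hypothesis before it. That probability cannot exceed the smallest stand-alone power in the chain, and it falls below it unless the tests always agree. Section 16.10 reports the stand-alone powers as the power planned for confirmatory testing at all times.

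The hypothesis hit hardest is the one that drives the sample size. Month 25 also carries particular weight: arm A is treated to month 15 (section 8.2.4), so months 7 and 13 are on treatment and month 25 is the only confirmatory fixed time off AOP2014. A reader relying on the stated 80% would misjudge how much a non-confirmed H4 says against the drug.

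**Working it through.** **Inputs (sections 16.1, 16.7, 16.10).** Two-sided alpha 0.05 for each test; RFS in arm B 55/50/45% and in arm A 75/70/65% at 7/13/25 months; n = 96 evaluable per arm; order H1, H2, H3, H4.

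**Step 1: reproduce the stated figures.** For the uncorrected chi-square test, power = Φ(k) with k = (0.20 − 1.96·s0)/s1, where s0 = √[2p̄(1−p̄)/n] and s1 = √{[pA(1−pA) + pB(1−pB)]/n}.

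- 7 months: s0 = √(0.455/96) = 0.0688, s1 = √(0.435/96) = 0.0673, k = 0.967, power 83.3% (stated 83%).
- 13 months: s0 = √(0.480/96) = 0.0707, s1 = √(0.460/96) = 0.0692, k = 0.887, power 81.2% (stated 81%).
- 25 months: s0 = √(0.495/96) = 0.0718, s1 = √(0.475/96) = 0.0703, k = 0.842, power 80.0% (stated 80%).
- Size: the same formula solved for 80% power at 45% against 65% gives 96 per arm, or 192; 192/0.9 = 213.3, rounded up to 214.
- Log-rank: expected events 96 × 0.55 + 96 × 0.35 = 86.4. Power is 81.8% (Schoenfeld) or 79.4% (Freedman), consistent with the stated value.

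All stated figures are therefore correct for each test alone.

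**Step 2: dependence between the fixed-time tests.** Relapse is absorbing, so for times s < t the covariance of the RFS proportions within an arm is S(t)[1 − S(s)]/n. Adding the two arms and dividing by the standard deviations gives:

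- 7 and 13 months: (0.70×0.25 + 0.50×0.45)/√(0.435×0.460) = 0.400/0.447 = 0.89
- 13 and 25 months: (0.65×0.30 + 0.45×0.50)/√(0.460×0.475) = 0.420/0.467 = 0.90
- 7 and 25 months: (0.65×0.25 + 0.45×0.45)/√(0.435×0.475) = 0.365/0.455 = 0.80

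These depend only on the protocol's rates at the three times.

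**Step 3: joint power by normal approximation.**

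- H1 and H2: Φ₂(0.967, 0.887; 0.89) = 77.4%.
- H1, H2 and H4, leaving out the log-rank gate: Φ₃(0.967, 0.887, 0.842) with the three correlations above = 72.9%.

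The second figure is a ceiling for H4, because the H3 gate can only lower it.

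**Step 4: full sequence by simulation.** Relapse times were piecewise exponential through the stated rates, with chi-square at 7, 13 and 25 months and log-rank to month 25 on the same patients (60,000 to 100,000 trials per run):

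| Hypothesis | Stated | Alone (simulated) | Through the sequence |
|---|---|---|---|
| H1, 7 months | 83% | 83–84% | 83–84% |
| H2, 13 months | 81% | 81% | 77% |
| H3, log-rank | slightly above 80% | 84% | 75–76% |
| H4, 25 months | 80% | 80% | 73% |

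**Step 5: sensitivity.** Changing when relapses fall within months 0 to 7 moves H3 between 73% and 77% and H4 between 72% and 73%. As outer limits, fully independent tests would give 68/54/43% for H2/H3/H4, and perfect dependence 81/80/80%. With no drop-out (107 per arm) the sequential figures are about 82%, 81% and 78%.

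**The case against.** The strongest reply is that no number in section 16.10 is miscalculated. Each sentence ties its figure to one named test, quoting per-test power under a fixed sequence is common, and the hierarchy is mentioned right beside the power claim. This stands as far as it goes: the fault lies in what the figures are said to represent, not in their calculation.

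Second, 192 evaluable at every analysis is the protocol's own worst case, with all drop-outs before month 6. If the 10% drop-out is instead spread evenly over 25 months (an assumption; mean evaluable about 209, 206 and 200), sequential power is about 81–82% for H2, 80% for H3 and 76–77% for H4. H2 and H3 then roughly meet their stated values and only H4 falls short. That is a fair qualification of the size. But 192 is the basis on which section 16.10 states its powers, and H4 misses 80% even with no drop-out.

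Third, the protocol describes its log-rank figure as a likely minimum, and the simulated stand-alone power is indeed nearer 84%. Even so, the gated figure on the planning case is about 75%.

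Fourth, the primary endpoint is RFS at 7 months, which is tested first and loses nothing. Months 13 and 25 are secondary, and estimates with confidence intervals are reported whatever the tests show. This limits the consequence but does not make the power statement correct.

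**Conclusion.** The concern holds. With 192 evaluable patients and the protocol's assumed rates, the power to confirm is 83% for H1, 77% for H2, about 75% for H3 and 73% for H4, against 83%, 81%, slightly above 80% and 80% as stated. In about 25% of trials in which the assumed effect is real, H4 would never be formally tested (1 − 0.75), and in about 27% it would not be confirmed (1 − 0.73).

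The H2 figure and the 73% ceiling for H4 follow from the stated rates alone. H3 depends modestly on the timing of relapses within the first 7 months. The shortfall shrinks if fewer patients are lost or are lost later, but for H4 it does not disappear at 214. The power of the primary hypothesis is unaffected.

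**What to change.** In section 16.10, state that the 83%, 81%, slightly above 80% and 80% figures are the powers of each test taken alone. Add that under the fixed sequence, with 192 evaluable patients, the power to reject is 83% (H1), 77% (H2), about 75% (H3) and 73% (H4), with H4 at about 78% if all 214 are evaluable. Replace the sentence claiming 80% at all times accordingly, and carry the same wording into the statistical analysis plan.

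The cost is a text change and slightly less favourable figures; enrolment, tests, significance level and order are untouched. Should the sponsor want 80% through H4, about 112 per arm would be needed: 224 evaluable, or 224/0.9 ≈ 249 randomized. That is optional and not needed to correct the statement.
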